### Intervention

The intervention will take place through face-to-face consultations in a reserved room at the State University of Rio de Janeiro by a team of nutritionists and physical education teachers. There will be 6 consultations. The first and the last with a 15-day break. The others were carried out monthly. The timeline of the interventions and the instruments used in the initial measurement and follow-up are described below in the SPIRIT timetable of the study presented in Fig. 2.

**Fig. 2 Fig2:**
[figure not shown]
Overview of the study period (SPIRIT Fig. 2013)

#### Nutritional guidelines on the healthy planetary diet

The nutritional guidelines will be based on the items that make up the Planetary Diet Index. They are nuts and peanuts; vegetables, fruits, and vegetables; whole grains; eggs; fish; tubers; milk and dairy products; vegetable oils; red meat; chicken; animal fat and added sugar. An adaptation of the proposal that will be used can be seen in Fig. 3.

**Fig. 3 Fig3:**
[figure not shown]
Adapted plan of the Planetary Healthy Diet for the Brazilian diet

As an incentive, the intervention group will receive throughout the intervention period a cookbook, a calendar of food goals, a booklet of guidance in relation to food, guidance regarding the purchase of healthy foods produced locally, the importance of buying food from the crop, and reducing loss and waste and reading labels.

Through a Food Frequency Questionnaire (FFQ), we will be able to better understand the daily life of the family and thus establish goals that the family must achieve, which will help adherence to PHD. Each month, the child and his family will be encouraged to choose one of the following goals: 1) reduce the consumption of ultra-processed foods, 2) increase the consumption of nuts, 3) try recipes with full use of foods, 4) reduce the consumption of red meat, 5) increase the consumption of whole grains, 6) increase the consumption of fruits, and 7) increase the consumption of vegetables and greens. A calendar will be provided every month, and stickers will be provided for the family to fill the days they can achieve the goals proposed by the professionals. It is a playful way for the child and their guardian to be encouraged to follow the proposed guidelines.

In addition to the goals, each meeting will be held as an educational activity with the child and their guardian. The first has already been tested by the research group in a previous study and is based on the degree of food processing and encouragement to purchase food at street markets [29]. The second activity aims to increase and diversify the consumption of fresh food purchased at street markets, encouraging a more active participation of children in their diet. The third activity is related to the consumption of whole grains. In addition, recipes and ludic activities to be carried out at home will be delivered to the participants.

The control group will receive general healthy eating guidelines based on those promoted in primary care for children with obesity and will also receive hyposodium herbal salt in the crossover design. Materials developed for the experimental group will be given to the control group at the end of the study.

#### Hyposodium salt

Herbal salt is composed of 25% potassium chloride (KCl) and 10% a mixture of rosemary, turmeric, basil, mint and oregano and will be delivered along with information on how to use it on the day of the first appointment. The placebo salt is a combination of regular salt and pink Himalaya salt.

#### Reduction of portion sizes

Children in the intervention group will be provided with utensils that encourage them to reduce the size of their portions: a soup plate with a colored border, a long and narrow glass and a bowl of reduced size [7]. Children will be instructed to eat all meals, when possible, on the utensils received.

Both the offer of salt and utensils aim to stimulate the domestic production of food, and, periodically, simple recipes will be offered to families.

#### Physical activity and sedentary behavior

The participants in the intervention group will receive a dance choreography video plus two or three gym class links available on YouTube each week to increase moderate-to-vigorous physical activity. On average, the duration of the video classes is 45 min. At the beginning of the intervention, a kit of sports materials containing ropes and balls and a booklet with information about the guidelines on physical activity and sedentary behavior for children and adolescents will be provided.

To improve adherence to the intervention, a set of motivational messages will be sent each week via WhatsApp, encouraging children to perform the activities. Additionally, children and their guardians will receive a list of goals to reduce sedentary time and increase physical activity throughout the research period, and they will choose two of them to achieve each week.

### Data analysis

The rate of change in the primary and secondary outcomes over time will be investigated by intention-to-treat analysis using mixed-effects models, which allow us to consider incomplete follow-up data and the correlation of repeated measures. The verification of the adequacy of the models will be done graphically through the diagnosis of the residues [30]. SAS software, version 9.4 (SAS Institute, Cary, NC, USA) will be used. In secondary analyses, with measurements of more than one family member, the correlation of the family cluster in the change estimates will be considered.

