**Methods:**

A factorial crossover design will also allocate families to receive reduced sodium salt plus anti-inflammatory herbs and a placebo salt. Both the control and intervention groups will be randomly assigned to the sequence of both salts. The approach aims to reduce body weight expectations and evaluate salt's impact on blood pressure. It includes a 1-month intervention, 1-month washout, and 1-month intervention with monthly clinic visits and teleservice by health professionals. The primary outcomes will be the variation in the Body Mass Index (BMI) of the children. BMI and the variation in the blood pressure of the pair (child/mother or father) as well as waist circumference (WC) and waist-to-height ratio (WHtR) will also be measured.

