#### Secondary objectives

Determine whether the use of low-sodium salt added to anti-inflammatory herbs reduces the blood pressure of child-guardian pairs.Determine if the family intervention promoted weight loss of the child-guardians.Investigate the effect of the intervention on total physical activity and sedentary time in children and guardians.

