### Design of the study

Factorial randomized clinical trial for the treatment of obesity with children between 7 and 12 years of age. Children and one of their guardians will be randomized to intervention with guidance regarding diet based on the PHD, on portion size reduction and a physical exercise program or control with general healthy eating guidance for a period of three months. The guidelines will be directed to all family members. Additionally, pairs in each arm will cross-receive a low-sodium salt added anti-inflammatory spices compared to a placebo salt (normal sodium content). The groups will be randomly subdivided into 4 groups of 27 individuals: 1 subgroup of the intervention group and 1 subgroup of the control group will receive hyposodium herbal salt, and the other 2 groups will receive placebo for 1 month. After 1 month of washout, the groups will receive the salt cross-label (Fig. 1). The protocol is reported according to the Standard Protocol Items: Recommendations for Interventional Trials (SPIRIT) [25].

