### Sample size and randomization procedure

The sample size of 48 pairs (child and one guardian) per group was calculated from a standard deviation for BMI equal to 3.0 and an expected difference of 1.72 units of BMI in the child [26] between the groups, considering a statistical power of 80% and significance level of 5%. This sample size of 96 pairs, 192 individuals plus an expected dropout of 10% of the participants make a final sample of 108 pairs (54 pairs in each group). After the recruitment phase, participants considered eligible will be randomly allocated to the control group or intervention group. The randomization will be performed in blocks of 8 individuals using a sequence of random numbers generated by a computer.

The necessary sample size for changes in blood pressure was based on data for adults (the guardians) of the *DASH (*Dietary Approaches to Stop Hypertension (Sacks et al.) and a Brazilian dietary intervention trial for adults [27]. The Brazilian trial focused on salt intake reduction, and after 6 months, systolic blood pressure was reduced by 14·4 mmHg and diastolic blood pressure by 9·7 mmHg in the experimental group compared with 6·7 and 4·6 mmHg, respectively, in the control group. A sample size of thirty-one subjects per arm (total 62) assumed a reduction in systolic blood pressure of 7·1 mmHg and a standard deviation of 10 mmHg [28] with a significance level of 5% and 80% power.

Therefore, the sample size for the change in BMI also allowed us to evaluate changes in blood pressure, at least for adults.

We used sequentially numbered, opaque paper bags with the salt and utensils given to the children´s family to preserve allocation concealment.

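### The single rate-of-change estimand, stated for all outcomes, does not measure the salt effect on blood pressure in the two-period crossover

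*Protocol article*

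**What the plan says.** The Data analysis section of the protocol article has one sentence on the estimand, and it covers primary and secondary outcomes together: "The rate of change in the primary and secondary outcomes over time will be investigated by intention-to-treat analysis using mixed-effects models". The reason given for mixed models is that they are models "which allow us to consider incomplete follow-up data and the correlation of repeated measures". The section adds residual diagnostics and an allowance for family clustering. It does not mention the salt, the period or the sequence.

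The first secondary objective is a salt question: "Determine whether the use of low-sodium salt added to anti-inflammatory herbs reduces the blood pressure of child-guardian pairs". The salt is compared by crossover within each lifestyle arm. The abstract gives the timing: "It includes a 1-month intervention, 1-month washout, and 1-month intervention with monthly clinic visits". Design of the study says: "After 1 month of washout, the groups will receive the salt cross-label". It also gives the allocation: "The groups will be randomly subdivided into 4 groups of 27 individuals", that is, lifestyle arm by salt sequence.

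The blood pressure sample size is a parallel two-arm calculation: "A sample size of thirty-one subjects per arm (total 62) assumed a reduction in systolic blood pressure of 7·1 mmHg", with a standard deviation of 10 mmHg, 5% significance and 80% power.

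**The concern.** A salt effect in this design is an on/off contrast within a person: blood pressure at the end of the low-sodium month against blood pressure at the end of the placebo month. A rate of change over follow-up is a different quantity. It blends a month on one salt, a washout month and a month on the other, with weights set by where the visits fall.

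This goes beyond unstated model detail. The article names an estimand and applies it to blood pressure, where it does not return the quantity that the objective asks for. If the sentence is followed as written, the trial may report a blood pressure slope that cannot be read as a salt effect in mmHg. Otherwise the contrast has to be chosen after the data are seen. The salt is one of the two randomised factors, and the Discussion expects public-health conclusions from it.

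**Working it through.** **Inputs from the protocol.** Blood pressure: difference 7.1 mmHg, SD 10 mmHg, 5% significance (two-sided assumed), 80% power. BMI: difference 1.72, SD 3.0. 96 pairs before the dropout allowance. Periods of one month, one month and one month.

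**Assumptions.** Visits at months 0, 1, 2 and 3 (the SPIRIT figure is not available), within-person correlation 0.5, no carry-over, no missing data.

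**The plan's own figures.**
- Blood pressure: n per arm = 2 × [10 × (1.960 + 0.842) / 7.1]² = 31.1. The stated 31 has 79.8% power, so it reproduces to rounding.
- BMI: 2 × [3.0 × 2.802 / 1.72]² = 47.8, so 48 per group. 48 / 0.9 = 53.3, so 54. Both are as stated.

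**Slope produced by a salt effect.** Let d be the size of the reduction. For times 0, 1, 2, 3 the mean is 1.5 and the sum of squares is 5, so the least-squares slope weights are −0.3, −0.1, +0.1, +0.3.
- Salt first, pattern (0, −d, 0, 0): slope = +0.1d per month. For 7.1 mmHg this is +0.71, the wrong sign.
- Salt second, pattern (0, 0, 0, −d): slope = −0.3d per month, or −2.13.

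**What each randomised slope comparison gives.**
- *Arm by time.* With balanced sequences, the salt adds (0.1d − 0.3d)/2 = −0.1d per month, or −0.71, to both arms, and cancels. In a 150-run simulation with 96 people, the arm-by-time term averaged −0.49 against a true lifestyle effect of −0.5 mmHg/month.
- *Sequence by time.* The difference is 0.1d + 0.3d = 0.4d, or 2.84 mmHg/month. Over three months this is 8.5 mmHg, which is not 7.1.

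**Dependence on the schedule.** The Intervention section describes six consultations, some at a 15-day interval. With visits at 0, 0.5, 1, 2 and 3 months, the sequence difference is 3.43 mmHg/month (0.48d). With visits at 0, 0.5, 1, 2, 2.5 and 3 months, it is 4.06 (0.57d).

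**Efficiency, visits at months 0 to 3.** The residual variance is 100 × (1 − 0.5) = 50.
- Crossover contrast: SE = √(2 × 50 / 96) = 1.02.
- Difference in slopes, 48 per sequence: SE = √(2 × (50/5) / 48) = 0.645.
- For a 3 mmHg effect (assumed): z = 3/1.02 = 2.94, about 83% power, against z = 1.2/0.645 = 1.86, about 46%.
- For the protocol's 7.1 mmHg, the slope difference has z = 2.84/0.645 = 4.40, about 99% power. At correlation 0.3 it is about 96%.
- The z ratio is 1.86/2.94 = 0.63. Squared, this is 0.4, so the slope comparison uses about 40% of the information in the contrast.

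**With a salt term.** In the same simulation, adding the salt received to the mixed model returned −7.05 mmHg (visit as a factor) and −7.14 (linear time) against a true −7.1.

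**Is the sample enough?** For a within-person contrast, N = [10√(2(1 − ρ)) × 2.802 / 7.1]². This gives a total of 22, 16, 10 or 7 for correlations of 0.3, 0.5, 0.7 or 0.8. With 96 completers, the detectable difference is about 3.4, 2.9, 2.2 or 1.8 mmHg. The planned sample is sufficient.

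**The case against.** The strongest reply is that the article commits only to mixed-effects models with repeated-measures correlation and lists no fixed effects, not even an arm term for BMI. Crossover terms are usually left to an analysis plan, and that plan is not shown. The outcomes are described as variations, so rate of change could mean change within each one-month period. This stands in part. The model class is suitable and the missing term list alone would be no finding. What remains is that the one stated estimand runs over time, is applied to blood pressure without distinction, and is nowhere tied to the salt periods.

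A reader might infer that the planned model cannot answer the blood pressure objective. The document does not support that: the same mixed-model framework recovers the effect once a salt term is present.

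A reader might also infer that a trend common to all families would be reported as a salt effect. One pooled slope would indeed be significant in about 87% of runs under an assumed common trend of −1 mmHg/month and no salt effect. But the protocol does not propose that analysis. It specifies intention-to-treat analysis of randomised groups, and a common trend cancels between sequences.

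The loss of power should not be overstated either. The 46% belongs to an assumed 3 mmHg and a four-visit schedule. At 7.1 mmHg the sequence comparison has about 99% power. On the six-visit schedule it reaches about 88% even at 3 mmHg. Without carry-over it is a valid test of the salt.

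**Conclusion.** The point holds as a wrongly fixed estimand for the salt factor. For blood pressure and urinary sodium/potassium, a rate of change over follow-up does not give the salt effect. Arm by time carries none of it. Sequence by time gives between 0.4 and 0.57 of it per month across the three schedules tried, with the wrong sign in the salt-first sequence. As a test, sequence by time remains valid without carry-over but is less efficient, at about 40% of the information for visits at months 0 to 3.

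The visit times and the within-person correlation are assumptions. The cancellation in arm by time needs balanced sequences and an equal salt effect in both arms. The defect does not reach the primary BMI comparison, the data to be collected or the sample size. It should be corrected before the blood pressure data are analysed.

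**What to change.** Split the Data analysis statement by question.

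- **BMI and other lifestyle outcomes:** keep the rate-of-change mixed model, with lifestyle arm by time as the effect of interest.
- **Blood pressure and urinary sodium/potassium:** state a crossover mixed model on the end-of-period values. Fixed effects are salt received, period, sequence, lifestyle arm (allowed to vary by period) and salt by arm. Random effects are person within family. Report the salt coefficient with its confidence interval, in mmHg for blood pressure, separately for children and guardians.
- **Period baselines:** adjustment is optional. The end-of-washout value is measured after randomisation and could reflect carry-over, so if it is used, say so in advance and give the unadjusted estimate as well.

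The salt and period terms are the essential part. The cost is one paragraph of analysis wording, with no new data, visits or participants.

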### Outcomes

#### Primary outcome

The primary outcome of the study will be the variation in the children's body mass index (BMI). Body weight will be measured on a portable electronic scale (Tanita BC-558). Height will be measured in duplicate with the use of a portable anthropometer of the brand Altura Exata. Both measurements will be measured with the assessed, barefoot, wearing light clothing, without props in the hair, with the arms extended to the side of the body, positioned by the horizontal plane of Frankfurt. The classification of nutritional status will be performed based on BMI/age values, in z scores, using the new curves of the World Health Organization with the use of the software WHO-Anthro Plus 2007 [31]. The values obtained will be classified according to the cutoff points recommended by the WHO for children over 5 years of age, being underweight: below –2Z; eutrophy: between –2 and + 1Z; overweight: between + 1 and + 2Z; obesity between + 2Z and + 3Z and severe obesity above 3Z of the reference median. This classification will be performed at baseline to confirm the inclusion criteria.

#### Secondary outcomes

Blood pressure will be measured with an electronic and digital device Omron® Hem 742, previously validated for use in children [32]. Before taking the measurement, it will be certified that the child or adolescent does not have a full bladder, has not ingested medications and/or coffee, has not eaten up to 30 min before the procedure and/or practiced physical exercises up to 1 h before. The measurement will be performed on the right arm, at the same level as the heart, supported on a table with a flat surface, with the palm of the hand facing up and the elbow slightly flexed. The individual should be seated, with feet in contact with the floor or flat surface platform, and remain in this position for 5 min at rest before the measurement [33]. Two BP measurements will be performed, with a minimum interval of 2 min, and the mean of the 2 measurements will be calculated. If the difference between the 2 measurements is greater than or equal to 5 mmHg, a new measurement will be taken.

The other secondary outcomes of the study investigated will be variations in the BMI of the responsible individual, waist circumference (WC), waist height ratio (WHtR), and urinary sodium/potassium.

The adult BMI is obtained through weight (kg) divided by height (m) squared. The values obtained will be classified according to the cutoff points recommended by the WHO for adults over 18 years of age, being underweight: below 18.5; eutrophy: between 18.6 and 24.9; overweight: between 25.0 and 29.9; grade I obesity: between 30.0 and 34.9; grade II obesity: between 35.0 and 39.9 and grade III obesity: above 40.0.

For the measurement of WC, a flexible and inelastic tape measure will be used, with an amplitude of 150 cm and a variation of 0.1 mm. WC will be measured with tape placed horizontally at the midpoint between the lower edge of the last rib and the iliac crest. The measurements will be performed with the tape firm on the skin, however, without compression of the tissues, being the evaluated standing with relaxed abdomen and with the arms extended to the side of the body. For the QC, the tape measure will be placed horizontally around the hip in the most protruding part of the buttocks [34]. The WHtR will be obtained by the ratio between WC and height, both in centimeters.

To measure urinary sodium and potassium, the spot urine method will be used [35]. A clean and sterile bottle will be provided. The participant will be instructed to open the bottle only at the time of collection to avoid contamination. The pot with the urine collected at any time of the day will be packed in Styrofoam and taken to the laboratory.

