## Abstract

**Background:**

Clinical trials to treat childhood obesity show modest results, weight regain and high dropout rates. Children with obesity often live in families with habits that contribute to unhealthy weight gain. This study will test whether a family intervention with a Brazilian-adapted Planetary Healthy Diet (PHD) and reduced portion sizes, along with increased physical activity and reduced sedentary behavior, can reduce excessive weight gain. The protocol promotes the intake of in natura products and water and reduces ultra-processed foods, sugar, and sodium. It encourages family lifestyle changes and physical activities, with randomized allocation to experimental and control groups. The responsible family member will be evaluated during follow-up. The control group will receive a print of the Brazilian dietary guideline.

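### Spot urine for sodium and potassium may be collected at any hour, which adds avoidable noise and leaves unadjusted concentrations open to dilution in the lifestyle comparison

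*Protocol article*

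**What the plan says.** All references are to the protocol article.

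- **Collection.** Secondary outcomes specifies a spot sample for urinary sodium and potassium, and on timing says: "The pot with the urine collected at any time of the day will be packed in Styrofoam and taken to the laboratory". It cites a reference for the method. The article itself describes no correction for urine concentration.
- **Outcome.** The same section lists "waist circumference (WC), waist height ratio (WHtR), and urinary sodium/potassium" among the secondary outcomes. It does not say whether the last item is a ratio or two separate measures.
- **Water.** The Background of the Abstract, describing the family intervention, says: "The protocol promotes the intake of in natura products and water and reduces ultra-processed foods, sugar, and sodium". Of the comparator it says: "The control group will receive a print of the Brazilian dietary guideline".
- **Salt comparison.** The Methods part of the Abstract says: "Both the control and intervention groups will be randomly assigned to the sequence of both salts". Every pair therefore receives both salts, one month each, with a one-month washout between them.
- **Salt composition.** Hyposodium salt gives 25% potassium chloride and 10% herbs for the herbal product.

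**The concern.** A spot sample yields a concentration, that is, excretion divided by urine volume. Concentration depends on the hour of voiding and on recent fluid intake as well as on what was eaten. Under the stated rule, one participant may give a morning sample in one salt month and an evening sample in the other, and that difference enters the salt contrast as error. The same spread enters the comparison of lifestyle arms.

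This matters because urine is the only objective marker of sodium intake in the article. The tools under Measures of adherence to intervention are a food frequency questionnaire, activity questionnaires, accelerometers and a report of exercise classes. None is specific to the trial salt, and the food questionnaire is given only at baseline and at the end, so it cannot separate the two salt months. If blood pressure does not move, urine is what would show whether the salt was used.

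Blood pressure, in the same section, is carefully standardised for bladder, coffee, food, exercise, posture and rest. Urine receives the opposite instruction.

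A second, conditional issue is dilution. If one lifestyle arm drinks more water, its sodium concentration can fall with no change in intake.

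**Working it through.** The article gives no sample size, variance or precision figure for urinary sodium or potassium, so there is no stated figure to reproduce, and the noise from free timing cannot be sized. What can be checked is the arithmetic of dilution and which comparison it touches.

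**1. Dilution at unchanged excretion.** Concentration = excretion / volume. If volume rises by a fraction x, sodium and potassium concentrations are both multiplied by 1/(1+x). The values of x are assumptions; the article gives none.

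| Volume rise | Change in concentration | Change in Na:K ratio |
|---|---|---|
| 10% | 1/1.1 − 1 = −9.1% | 0% |
| 20% | 1/1.2 − 1 = −16.7% | 0% |
| 30% | 1/1.3 − 1 = −23.1% | 0% |

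The ratio does not change because the factor 1/(1+x) appears in both numerator and denominator.

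**2. Consequence if raw concentrations were compared between lifestyle arms.** Inputs: 48 per arm (Sample size and randomization procedure), two-sided 5% test on log concentration, assumed log-scale SD s of 0.4 to 0.6, no true difference in intake. The shift is ln(1+x), and the chance of a significant result is Φ(d − 1.96) + Φ(−d − 1.96), with d = ln(1+x) / (s√(2/48)).

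For x = 20% and s = 0.5: d = 0.182 / 0.102 = 1.79, giving about 43%. Over s from 0.6 to 0.4 the chance is about 12-22% at +10% volume, 32-61% at +20% and 57-90% at +30%, against a nominal 5%. These figures depend entirely on the assumed volumes and SDs.

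**3. Which comparison is exposed.** Lifestyle advice applies throughout, so within each lifestyle arm it covers both salt periods, and salt sequence is randomised within arm. Water advice is therefore largely balanced between salts. In the salt contrast, free timing acts mainly as noise. The directional risk is confined to the lifestyle contrast.

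**4. Why the ratio cannot stand alone.** If sodium excretion is unchanged and potassium excretion rises by a fraction y, the ratio is multiplied by 1/(1+y). A 10-30% rise in potassium (again assumed) lowers the ratio by 9-23% with no change in sodium. The potassium chloride in the herbal salt can raise potassium, and so can the fruit, vegetables and nuts among the monthly goals. Reporting both ions helps to tell the cases apart: dilution lowers both, whereas the herbal salt would be expected to raise potassium.

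**The case against.** The strongest objection is that no directional bias is shown. Most of it stands.

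- **The outcome may already be the ratio.** The listed wording allows that reading, and dilution then cancels. It equally allows two separate measures, since the collection text names sodium and potassium individually. The article does not settle it.
- **No raw comparison is stated.** Data analysis describes mixed-effects models in general terms. A creatinine correction or a conversion to 24-hour excretion may be in the cited method or the full protocol, neither of which is shown. Its absence from an article is not a fault.
- **The water contrast is thinly documented.** It rests on one sentence of the Abstract. Water is not among the diet items or the seven monthly goals, and control families also receive healthy-eating guidance whose content on water is not shown.
- **Nothing suggests that collection time differs by arm or by salt.** Free timing is therefore a source of noise, not a demonstrated bias.

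A reader might infer that the intervention's urinary sodium result is biased in its favour as the plan stands. For these reasons the documents do not support that.

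The timing rule survives all of this. It is stated outright, so it is not a detail left to another document, and a later correction for concentration would not restore a common collection time.

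**Conclusion.** The point holds as one of precision, with a conditional warning attached. Collection at any hour adds avoidable variation to the salt and lifestyle comparisons of urinary sodium and potassium; its size cannot be given from the article. A fall of about 9-23% in sodium concentration without lower intake could arise in the lifestyle comparison, but only if raw concentrations are compared, the intervention arm drinks more than control, and urine volume rises by the assumed 10-30%. It does not arise if the outcome is the ratio.

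A reader might also set the 9-23% against the sodium reduction in the herbal salt (100 − 25 − 10 = 65% sodium chloride if the remainder is all sodium chloride, hence 35% less) and conclude that dilution could account for a large share of the signal. That comparison is not valid. The 35% belongs to the salt contrast, where water advice is largely balanced, while the dilution effect belongs to the lifestyle contrast, where both arms receive both salts.

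Only a secondary outcome is concerned. The primary outcome, child BMI, and blood pressure are unaffected.

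**What to change.** - **Timing.** Replace the free collection time with one clock window, the same for a given participant at every visit; a sample voided at the clinic visit would do.
- **Outcome.** State whether the urinary outcome is the sodium:potassium ratio or separate values. Do not base the lifestyle comparison on unadjusted concentrations; use the ratio or another dilution-corrected value, such as a creatinine-adjusted one.
- **Reporting.** Report sodium and potassium separately beside the ratio, and state that a fall in the ratio alone will not be taken as lower sodium intake.

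The cost is one instruction to families and a few lines in the analysis plan; creatinine adjustment, if chosen, would also need that assay. The downside is slightly less flexible collection for families. The timing change has to be made before samples are taken, because it cannot be repaired afterwards.
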